### Participants: selection of cases & controls

#### **
*CC1 & CC2*
**

*Population of dead cases (A)* All women who died of primary breast cancer (as stated in part 1 of the death certificate) age 47–89, within the specified 2-year study period will be selected. Cases of women with only in situ primary breast cancer records (i.e. no invasive record) will be included, but Death Certificate Only (DCO) cases will be excluded. Case A women will have had their date of first diagnosis of primary breast cancer (in situ or invasive) age 47–89 and since 1990, and for subsequent phases of this evaluation (main phase onwards), they will not have been included as cases in previous evaluation periods, although they may have been included as controls, and may also be selected as a case C in the same evaluation.

*Population of cases A-matched general population controls (B)* For each case A, two women will be selected among the general population in the Health & Social Care Information Centre (HSCIC) database at Exeter who, are registered in the same National Health Applications and Infrastructure Services (NHAIS) system as the case at the case’s date of first diagnosis, are alive at the case’s date of death, and were born within 1 month either side of the case’s date of birth. Control B women may have had primary breast cancer (in situ or invasive) at the case’s date of first diagnosis. For subsequent phases of this evaluation (main phase onwards), they will not have been included as population controls B, E, or D in previous evaluation periods, although they may be included as a controls E or D within the same evaluation period.

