*Population of cases A-matched diseased controls (E)* For each case A, one woman will be selected among the CR population who was alive at the case’s date of death, and was born within 1 month either side of the case’s date of birth. DCO cases will be excluded. Control E women will have had primary invasive breast cancer diagnosed within 2 months prior to *and including* the case’s date of first diagnosis and: this is necessary to ensure that the control survived for at least as long as the cases. She will have been registered in the same Cancer Network (CN) at the case’s date of first diagnosis. If no control E is found using this criterion, the date range will be expanded to 3 months prior to the case’s date of first diagnosis (or 6 months prior, if the case’s age at first diagnosis is less than 50 or over 70). For subsequent phases of this evaluation (main phase onwards), they may have been included as population controls B or D in previous or within the same evaluation periods, and may be included as a case C within the same evaluation period.

#### **
*CC3a, CC3b & CC4*
**

*Population of incident cases (C)* All women who have had primary breast cancer (in situ or invasive), diagnosed age 47–89 within the specified 2-year study period will be selected. The **index diagnosis** will be either a first or a subsequent tumour and, therefore, women may have had a previous history of in situ or invasive primary breast cancer (i.e. prior to the date of their index diagnosis). Case C women may have died from primary breast cancer (as stated in part 1 of death certificate) age 47–89 during the specified 2-year study period, or afterwards. Cases of women with in situ primary breast cancer records only (i.e. no invasive record) will be included, but DCO cases will be excluded. For subsequent phases of this evaluation (main phase onwards), they will not have been included as cases in previous evaluation periods, although they may have been included as controls, and may also be selected as a case A in the same evaluation.

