*Population of cases C-matched general population controls (D)* For each case C, two women will be selected from the general population in the HSCIC database at Exeter who, are registered in the same NHAIS system as the case at the case’s date of index diagnosis, are alive at case’s date of index diagnosis, and were born within 1 month either side of the case’s date of birth. For subsequent phases of this evaluation (main phase onwards), they will not have been included as population controls B, E, or D in previous evaluation periods, although they may be included as controls B or E within the same evaluation period.

Incident cases (C) and matched general population controls (D) will be selected *a posteriori* by the PRU, using tumour information, to suit the purpose of each case-study (see Figure 1).

**For CC3a**, incident cases (C) will be restricted to those women with invasive breast cancer, and matched general population controls (D) will be restricted to those women who have never had invasive primary breast cancer, but may have had in situ primary breast cancer prior to *and including* the case’s date of index diagnosis.

**For CC3b**, all incident cases (C) will be selected. For in situ cases, matched general population controls (D) will be restricted to those women who never had primary breast cancer (in situ or invasive) prior to *and including* the case’s date of index diagnosis; for invasive cases, to those women who never had invasive primary breast cancer, but may have had in situ primary breast cancer.

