**For CC4**, incident cases (C) will be restricted to those women with advanced stage (defined below) primary breast cancer, and matched general population controls (D) will be restricted to those women who have never had advanced stage primary breast cancer, but may have had in situ or early stage primary breast cancer prior to *and including* the case’s date of index diagnosis. Breast cancer will be defined as “advanced stage” if tumour size is larger than 20 mm, or if at least one regional lymph node is affected, or if both, and as “early stage” if tumour size is equal to or smaller than 20 mm and no regional lymph node is affected. For the purpose of data collection, we have used an inclusive definition of “advanced stage”, but we will also analyse the data by Stage to assess the association between screening and metastatic breast cancer for instance, and using only those cases which are node positive, as this is generally accepted as an important prognostic factor and as a predictor of the effect of screening on mortality (Smith et al., 2004 [10]).

If no matched control is found for a particular case (A or C) with a date of birth within 1 month either side of the case’s date of birth, the range will be expanded to 3 months either side (or 6 months either side if the case’s age at index diagnosis of primary breast cancer is under 50 or over 70).

All cases and controls will appear on the HSCIC database at Exeter. We will aim to select female cases and controls who have been registered with the NHS by age 47 (determined by either date of first registration on local NHAIS system or prior cervical/bowel screening history), and have had available data on both breast and cervical (for women aged 47–64), and, possibly bowel (for women aged 60–69) screening strictly prior to their date of first diagnosis/pseudo-diagnosis (that is, they have been invited to screening at least once), although this may not be practicably feasible for dead cases and matching controls with older age at death. Patient breast, cervical, and bowel (for the main phase) screening history, primary breast tumours attributes and treatment data will be retrieved for all cases and controls, as well as deprivation quintile.

A detailed description of the algorithm to be used for the selection of cases and controls is available from the authors.

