Once diagnosed with breast cancer, the cases come under clinical management and do not continue with routine breast screening as before. The controls, however, may continue to attend screening up to the time of the case being entered into the study. This potential bias is addressed at the design stage by giving the controls a pseudo-diagnosis date that is the same as that of their matched case and screening history is only considered up to that date (Connor et al., 2000 [14]). This is in fact an over-correction and results in a bias *against screening*. The fact of the case having necessarily a diagnosis of breast cancer and a control usually not having such a diagnosis, induces an artificially higher retrospective probability of screening exposure in the cases, a bias *against screening* (i.e. the screen-detected cases will always have this screen recorded at diagnosis, whereas the large majority of controls will not at pseudo-diagnosis). Simply excluding the detection screens from the histories would bias the results *in favour of screening*. When assessing the effect of ever having been screened, the major driver of this bias is prevalence screening, and for a mature programme with approximately 6 incidence screens for each prevalence screen, this bias is likely to be small. However, this bias may remain when using other measure of screening exposure. The extent of screening opportunity bias will be investigated by applying an analytical correction to the odds ratio using the method by Duffy et al., 2008a [15], and by performing sensitivity analyses in which the date of pseudo-diagnosis for controls will be extended by up to 4 years, the estimated average sojourn time for each screen-detected case, to counteract the artificially higher retrospective probability of screening exposure in cases (Connor et al., 2000 [14]).

But the major sources of bias in case–control studies are potential self-selection and lead-time biases (Puliti et al., 2011 [16]). Length bias will also be discussed. Note that lead-time and length biases will only affect analyses assessing the effect of screening on survival among cases (i.e. case-study 2), but not those assessing its impact on population outcomes (incidence or mortality).

#### **
*Self-selection bias (or non-compliance bias)*
**

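### In CC3a, CC3b and CC4 the cancer-history restriction placed on controls is not placed on cases, which biases the time-since-last-screen odds ratios downwards

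*Protocol article*

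**What the plan says.** All references are to the protocol article.

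- **Cases.** Under Participants: selection of cases & controls, the index tumour of a case C may be a first or a later one, and "women may have had a previous history of in situ or invasive primary breast cancer (i.e. prior to the date of their index diagnosis". The later selection looks only at the index tumour: invasive for CC3a, advanced stage for CC4, and for CC3b "all incident cases (C) will be selected".
- **Controls, CC3a.** They are "restricted to those women who have never had invasive primary breast cancer, but may have had in situ primary breast cancer prior to" or on the case's index date. The invasive sets of CC3b follow the same rule.
- **Controls, in situ sets of CC3b.** They are "restricted to those women who never had primary breast cancer (in situ or invasive) prior to" or on the index date.
- **Controls, CC4.** "matched general population controls (D) will be restricted to those women who have never had advanced stage primary breast cancer"; earlier in situ or early-stage disease is allowed.
- **Exposure window.** Study design & objectives counts screening before the index diagnosis in all three studies. The Participants paragraph on NHS registration by age 47 speaks instead of the first diagnosis or pseudo-diagnosis.
- **Screening after a diagnosis.** Bias & Effect modification, on exposure opportunity, says that once diagnosed "the cases come under clinical management and do not continue with routine breast screening as before".

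**The concern.** A control should be a woman who would have been a case had she been diagnosed on the index date. Here a woman with an earlier invasive cancer can enter CC3a as a case if she develops a second invasive tumour, but she can never enter as a control. The years between her two tumours count as screening opportunity, although on the protocol's own account she was no longer screened as before. Women with that history are removed from the comparison group.

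The pseudo-diagnosis date does not cure this. It aligns the end of the window at the index tumour and does nothing about an interruption caused by a previous one. The bias section does not discuss the asymmetry.

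Most is at stake in CC3a/b. The Statistical methods section singles out time since last screen there, and estimates overdiagnosis from the excess risk at screened ages and the compensating deficit at older ages. Odds ratios biased downwards shrink the excess and deepen the deficit, and both push estimated overdiagnosis down. The size of the main phase gives precision but does not remove the bias.

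**Working it through.** **Step 1. Compare the rules set by set.**

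| Set | Case filter | History barred in controls | History allowed in controls | History found among cases only |
|---|---|---|---|---|
| CC3a | index tumour invasive | invasive | in situ | invasive |
| CC3b, invasive | none on history | invasive | in situ | invasive |
| CC3b, in situ | none on history | any breast cancer | none | any breast cancer |
| CC4 | index tumour advanced | advanced stage | in situ, early stage | advanced stage |

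The last column is the defect. It differs by study and is narrowest in CC4.

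**Step 2. Size for screening within 3 years (a secondary measure).** The document states no figure for these studies that could be reproduced, so this is an illustration. Let p be the exposure in controls, f the share of cases with a barred history, and q the exposure in those cases. With no true effect,

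case exposure = (1 − f)p + fq; OR = odds(case exposure) / odds(p).

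All inputs are assumptions: p = 65%, f = 3–8%, q = 5–30%. The control odds are 0.65/0.35 = 1.857.

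- f = 3%, q = 30%: 0.97 × 0.65 + 0.03 × 0.30 = 0.6395; odds 1.774; OR 0.955.
- f = 5%, q = 15%: 0.95 × 0.65 + 0.05 × 0.15 = 0.625; odds 1.667; OR 0.897.
- f = 8%, q = 5%: 0.92 × 0.65 + 0.08 × 0.05 = 0.602; odds 1.513; OR 0.814.

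A wider grid (p = 60–70%, q = 0–30%) gives 0.94–0.98 at f = 2%, 0.85–0.94 at f = 5% and 0.73–0.88 at f = 10%. At f = 5% on that grid, a true OR of 1.20 is seen as 1.00–1.12.

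**Step 3. Above screening age.** Few women on either side then have a recent routine screen. With p = 10% (assumed), f = 8%, q = 5%: 0.92 × 0.10 + 0.08 × 0.05 = 0.096; odds 0.1062 against 0.1111; OR 0.956.

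**Step 4. Ever attended (the primary measure).** Take p = 77%, the coverage the article quotes for ages 53–70, as control exposure (an assumption), and f = 5%.

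- q = 50%: 0.95 × 0.77 + 0.05 × 0.50 = 0.7565; OR 0.928.
- q = 90%: 0.95 × 0.77 + 0.05 × 0.90 = 0.7765; OR 1.038.

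An earlier cancer does not erase earlier attendance, so the sign depends on whether these women were ever screened more or less often than others.

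These are unmatched odds ratios; the planned analysis is conditional. Setting f = 0 through a common history rule removes the distortion in every scenario.

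**The case against.** The strongest reply is that the asymmetry is partial and its effect unmeasured. Much of this stands.

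- A reader might infer that controls in all three studies are free of earlier breast cancer, so that women who have left routine screening appear among cases only. The text does not support that: only the in situ sets of CC3b are so strict. Elsewhere, women with in situ disease, and in CC4 also early-stage disease, may be on both sides.
- The relevant f is the share with a barred history, not the share of all second tumours. It can be smaller than the values assumed above, above all in CC4.
- A reader might set the shift in the odds ratio beside the 3.3–10% overdiagnosis range in the Background. That range is a percentage of expected cumulative incidence from age 50 to 79 after bias correction. The scales differ, and no such comparison is made here.
- A reader might see the same fault in CC2, where "Cases of women with only in situ primary breast cancer records (i.e. no invasive record) will be included" but diseased controls must have invasive cancer. Exposure there stops at the case's first diagnosis, so an earlier tumour cannot cut her history short. That mismatch is a separate comparability question.

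It can also be said that the detailed selection algorithm is available separately and might contain the missing filter. This carries less weight. The article expressly admits later tumours and takes every case C into CC3b, so such a filter would contradict its stated rule.

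**Conclusion.** The point holds in limited form. The article fixes unequal history rules for cases and controls, and its own account of screening after diagnosis supplies the route to bias. The direction is downwards for recent screening, provided that women with an earlier barred cancer have fewer routine screens in the last 3 years than other women. The magnitude, roughly 0.81–0.96 for a true value of 1.00, rests wholly on assumed values of p, f and q; the article says only that screening does not continue as before and gives no rate. No directional claim can be made for ever attending, and no size can be put on the overdiagnosis estimate itself.

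**What to change.** At the a posteriori selection step, require each case to meet, just before her index diagnosis, the restriction her controls must meet:

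- CC3a and invasive sets of CC3b: no earlier invasive cancer;
- in situ sets of CC3b: no earlier breast cancer;
- CC4: no earlier advanced-stage cancer.

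Report the excluded second-tumour cases as a separate or sensitivity analysis. Also reconcile the index-diagnosis wording in Study design & objectives with the first-diagnosis wording in Participants.

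No new variables are needed: Table 1 already lists status, date, size, nodes and stage for all primary breast tumours. The cost is a small share of cases. At an assumed 3–8%, that is 42–112 of the 1400 planned pilot cases (0.03 × 1400 to 0.08 × 1400), and fewer where the barred history is rarer.

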### Setting & source population

The background, implementation and organisation of the NHSBSP are described in detail elsewhere (Advisory Committee on Breast Cancer Screening, 2006 [9]). For this study, all women who were invited to participate in the breast screening programme in England (from 1988 onwards), and who did not express dissent to their records being used for evaluation purposes, will be targeted.

The evaluation will begin with a pilot phase in collaboration with the Knowledge & Intelligence team London, KIT London (formerly Thames Cancer Registry), using cases that died from or were diagnosed with breast cancer between 1st of January 2008 and 31 of December 2009 in London. The main phase of the study will then be undertaken, which will cover the whole of England or, in the case of CC2, those regions (i.e. previous cancer registries) for which tumour attributes and treatment variables will be available from 1st of January 2010 - in collaboration with the Office for National Statistics (ONS). Each main phase evaluation will cover a 2-year period.

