Women who accept the invitation to screening (attenders) may have an a priori better health status (and a lower underlying risk of dying from breast cancer) compared with women who do not (non-attenders), and therefore are less likely to die from the disease. We would anticipate that this will confer a bias *in favour of* screening. Although this bias in favour of screening is unavoidable at the design stage, it can be approximately corrected for in the statistical analysis. In women diagnosed with breast cancer aged 47–52 (and their controls) we will look at two factors: “(invited and) screened”, “invited but not screened” compared to “not invited”. The odds ratio in “invited but not screened” can be used to adjust for the self-selection bias using the method by Duffy et al. (2002) [6]. This method cannot be used in older women as they will all have been invited.

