The method developed by Duffy et al. (2002) [6] will also be used to correct the estimated odds ratio using data on participation in the NHSCSP (cervical) and/or NHSBCSP (bowel) screening programmes, rather than data on participation from the RCTs of mammographic screening. In the absence of self-selection, the relative risk of primary breast cancer (death/incidence) associated with breast screening for non-attenders at cervical or bowel screening would be expected to be equal to the relative risk in cervical or bowel screening attenders (after adjusting for breast cancer screening). In practice, the relative risk of primary breast cancer has been shown to be about 10% lower in non-attenders to RCTs (Duffy et al., 2002 [6]). The crucial element in correcting for self-selection bias is the risk ratio (termed “Dr”) for non-attenders versus attenders to cervical or bowel screening. This will be calculated for women who attended breast screening at least once and for women who did not attend a single screen, to control for attendance at breast screening. A range of denominator values for “Dr” will be assessed for sensitivity. One could compare primary breast cancer rates (i) in women who have had bowel/cervical screening - but not breast screening -with women who have had neither bowel/cervical nor breast screening; and (ii) in women who have had *both* bowel/cervical and breast screening with women who have only had breast screening. Data for women with age at diagnosis/ pseudo-diagnosis between 47 and 64 year-old who would have been invited to both the breast and cervical screening programmes will be used. Alternatively, data for women with age at diagnosis/pseudo-diagnosis between 60 and 69 year-old who would have been invited to both the breast and bowel screening programmes will be used. Also, in women under age 50, one could compare primary breast cancer rates in women who have, or have not had, cervical screening, hence by-passing the positive confounding between uptake of the various screening programmes.

Breast screening coverage of women aged 53–70 in England was 77% at 31st March 2012 (The HSCIC Breast Screening Programme – England report, 2011-2012 [17]).

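### The aim of selecting only women already invited to screening conflicts with the planned self-selection correction at ages 47–52, which needs uninvited women as its reference

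*Protocol article*

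**What the plan says.** The protocol article describes who enters the study in three places.

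- **Setting & source population** targets "all women who were invited to participate in the breast screening programme in England (from 1988 onwards"). It gives no timing relative to diagnosis.
- **Participants: selection of cases & controls**, in the paragraphs defining groups A, B, E, C and D, uses age, dates of diagnosis and death, cancer history, registration area and date of birth. Invitation is not a condition for any group.
- **The closing paragraphs of that section** add an aim for all cases and controls. It begins "We will aim to select female cases and controls who have been registered with the NHS by age 47" and goes on to require that they "have had available data on both breast and cervical (for women aged 47–64") and possibly bowel screening, strictly before the diagnosis or pseudo-diagnosis date, with the gloss "that is, they have been invited to screening at least once". The one relaxation is "although this may not be practicably feasible for dead cases and matching controls with older age at death".

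Under **Bias & Effect modification**, the self-selection section plans a correction for women aged 47–52 at diagnosis and their controls. It compares two groups, women screened and women invited but not screened, with women not invited. The odds ratio for the second group feeds the correction. On the limits of the method it says: "This method cannot be used in older women as they will all have been invited". The same section offers an option: "in women under age 50, one could compare primary breast cancer rates in women who have, or have not had, cervical screening", with the stated purpose of avoiding the confounding that arises because uptake of the different programmes is correlated.

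**The concern.** A woman who meets the selection aim has, by its own gloss, been invited before her diagnosis or pseudo-diagnosis date. She therefore cannot belong to the uninvited group at that date. The 47–52 correction needs that group as its reference, and 47–52 is the only age range for which the protocol considers the method usable.

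At stake is the one planned contrast that sets breast-screening non-attenders directly against uninvited women within the English programme. The other planned corrections use attendance at cervical or bowel screening as a proxy for self-selection, and this contrast could serve as a check on them. Timing matters: women left out at extraction cannot be recovered at analysis, and the evaluation is to be repeated every two years.

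**Working it through.** The protocol gives no figure for this analysis, and no count of women aged 47–52 by invitation status, so there is nothing to reproduce. The check sets the statements side by side and then asks what can be estimated.

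**Step 1: does the aim cover ages 47–52?** The breast-and-cervical element is stated for ages 47–64, which includes 47–52. The relaxation concerns older ages at death and does not exempt this age range. The gloss on invitation names no programme, but it explains the availability of data on both breast and cervical screening. An invitation to cervical screening alone would not satisfy it.

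**Step 2: does the source-population statement exclude these women by itself?** No. A woman uninvited at her pseudo-diagnosis date but invited later still satisfies it. The exclusion comes from the requirement in the Participants section that the invitation precede that date.

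**Step 3: what can be estimated?** Let *s* = 1 for screened women and *n* = 1 for women invited but not screened, with uninvited women as the reference (*s* = *n* = 0). With an intercept, the distinct design rows are:

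- screened: (1, 1, 0)
- invited, not screened: (1, 0, 1)
- not invited: (1, 0, 0)

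All three rows together have rank 3, so both odds ratios can be estimated. Without the third row the rank is 2.

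Conditional logistic regression gives the same answer. If every woman has been invited, *s* + *n* = 1 for everyone, and the contribution of each woman is

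exp(β₁*s* + β₂*n*) = exp(β₂) × exp[(β₁ − β₂)*s*].

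The factor exp(β₂) is common to all members of a matched set and cancels. Only β₁ − β₂, screened versus invited but not screened, is identified. The coefficient that feeds the correction is β₂, and it is not identified.

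**Step 4: what if the aim is only partly met?** Then β₂ can be estimated from whichever uninvited women remain. They would be the women for whom the selection aim failed, not a designed comparison group, and their number cannot be derived from the document.

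**Step 5: the under-50 option.** Comparing women with and without cervical screening remains possible among invited women. But if all of them have been invited to breast screening, breast-screening uptake varies among them, and the confounding that the option was meant to avoid returns.

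**The case against.** The strongest reply is that the invitation wording is an aim, hedged for feasibility, whereas the operative definitions take all eligible cases and set no invitation condition for controls. Naming an uninvited category suggests that the investigators expected such women in the data. The article also says that a detailed selection algorithm can be obtained from its authors, and that algorithm may already deal with ages 47–52.

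Much of this stands. A reader might infer that the protocol keeps only invited women; the text does not go that far. A reader might also infer that the promised improvement in handling self-selection is lost and that the study must fall back on factors from the old screening trials. The document does not support that. The improvement it promises, in the Abstract and Background, is the method using data from other screening programmes. That method needs no uninvited group and is put forward as a replacement for the trial data. Individual-level adjustment for participation in other programmes is planned as well. The under-50 comparison is worded as a possibility, not a commitment.

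What the reply does not remove is the conflict in the published text. If the group definitions govern, they disagree with the stated aim; if the aim governs, it undercuts the 47–52 analysis. An unseen algorithm may settle the matter, but the article states both a selection aim and an analysis that the aim works against.

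**Conclusion.** The conflict is real but limited in reach. The selection aim, with no exemption for ages 47–52, is at odds both with the group definitions and with a planned analysis that depends on uninvited women. To the extent that the aim is met, the study creates at 47–52 the very condition under which the protocol itself rules the method out at older ages.

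In size, one of several planned self-selection corrections becomes inestimable if the aim is fully met, and rests on an unplanned residue of women if it is partly met. One optional comparison under age 50 loses much of its rationale. The cervical/bowel correction, the regression adjustment and the primary odds ratios are not affected.

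This rests on two readings: that the invitation gloss includes breast screening, and that invitation status is judged at the diagnosis or pseudo-diagnosis date. The wording supports both. The point should be settled before extraction.

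**What to change.** 1. In the closing paragraphs of the Participants section, state that the breast-invitation criterion does not apply at selection to cases aged 47–52 at diagnosis and their matched controls.
2. Record each woman's breast-screening invitation status at the diagnosis or pseudo-diagnosis date.
3. Align the source-population statement with this, so that women not yet invited at that date are clearly eligible at these ages.
4. If any primary analysis is to be restricted to invited women, say so and specify how the restriction preserves matched sets. Dropping individuals one by one could leave cases without controls or controls without a case. Such a restriction is not needed to resolve the conflict.

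The cost is a change to the selection wording and algorithm plus one recorded variable. The downside is that some sets at ages 47–52 will contribute little to the ever-attended contrast and will serve mainly the self-selection estimate.
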